### Secondary outcome measures

The secondary outcome measures to be assessed at baseline, 6, 12, and 18 months (unless stated) will include: changes in lower limb functional muscle strength and power, isometric knee extensor, dorsi-flexor and hand grip strength, dynamic balance and reaction time, gait, Instrumental Activities of Daily Living (IADL), quality of life, cognitive function and falls- related self-efficacy (Table 2).

#### Functional muscle strength and power

Functional muscle strength of the lower extremities will be assessed using the 30-second Sit-to-Stand (STS) test. Participants will start from a seated position in a chair, with arms folded across the chest, and will be instructed to stand fully upright and return to the seated position as many times as possible in 30 seconds. The final score will be the number of complete stands recorded during this time. The STS test has been shown to have a good test-retest reliability correlation of 0.84 to 0.92 in a sample of community-dwelling men and women over the age of 60 years [51].

Functional lower limb muscle power will be assessed using five consecutive sit-to-stands [52]. Participants will be fitted with a tri-axial accelerometer (x-BIMU Bluetooth Kit, x-io Technologies Limited, Ascot, UK, gyroscope ±2,000°/s, accelerometer ±16 g, 16-bit A/D conversion, sampled at 256 Hz) at the right hip, and will be instructed to perform each STS as rapidly as possible. For each complete STS, the mean concentric power relative to body weight (W/kg) will be calculated based on the product of acceleration and velocity in line with previous research [52].

#### Isometric muscle strength

Bi-lateral maximal isometric knee extensor strength will be measured using Lord’s strap assembly incorporating a strain gauge (Neuroscience Research Australia, Sydney, Australia). Briefly, participants will be seated with their hip and knee at an angle of 90°, with a strain gauge attached to a strap around the leg about 10 cm above the ankle joint. A strap will also be placed around the thighs to prevent movement of the pelvis and minimise any contribution of the gluteal muscles. Participants will be asked to perform 2 practice trials prior to the completion of 2 maximal efforts with a 60-second rest between each test. For analysis, the maximal knee extensor strength (kg) of each leg will be expressed per unit of lower leg length to compensate for the length of the lever arm. This test has been shown to have excellent test-retest reliability (Pearson’s r = 0.92) [53].

Bi-lateral maximal isometric dorsi-flexion strength will be assessed using a dorsi-flexion dynamometer (Neuroscience Research Australia, Sydney, Australia). Participants will be instructed to sit on a 45-cm high chair with the foot strapped securely to a spring-gauged plate attached to a strain gauge load cell. Participants will be instructed to perform 1 practice trial followed by 2 maximal effort muscle contractions, interspersed by a 10- to 15-second rest [54]. For analysis, maximal dorsi-flexion strength (kg) of each leg will be recorded.

Bi-lateral maximal isometric grip strength will be assessed using a hand-held dynamometer (Jamar dynamometer, Asimov Engineering Co., Los Angeles, CA, USA). Participants will be instructed to sit on a standard height chair with their shoulder adducted and neutrally rotated, elbow flexed at 90°, forearm neutral and hand slightly extended. They will be instructed to perform 1 practice trial, followed by 2 maximal effort muscle contractions by squeezing the handle of the dynamometer as forcefully as possible. For analysis, maximal grip strength (kg) of each hand will be recorded.

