**Table 2 Tab2:** **Summary of the outcome measures**

**Outcome measures**	**Data collection method**	**Data collection points**			
		**Baseline**	**6 months**	**12 months**	**18 months**
Primary outcome measure					
Falls	Monthly falls calendars	Monthly			
Secondary outcome measures					
Muscle power	5-consective sit-to-stands	x	x	x	x
Muscle strength	30-second Sit-to-Stand test	x	x	x	x
	Isometric knee extensor strength	x	x	x	x
	Isometric dorsi-flexion strength	x	x	x	x
	Hand grip dynamometer	x	x	x	x
Muscle function and balance	Timed up-and-Go: single- and dual-task	x	x	x	x
	Four-squared step test	x	x	x	x
	Choice reaction time	x	x	x	x
Single- and dual-task gait	Gait (4.9 m electronic walkway): gait velocity, cadence, step length, double support time, stride wide and dual-task cost	x	x	x	x
Instrumental Activities of Daily	Lawton IADL questionnaire	x	x	x	x
Living (IADL)					
Health-related Quality of Life	Short Form (36) version 2 questionnaire and the Assessment of Quality of Life - 6D scale	x	x	x	x
Cognitive function	CogState Brief Battery computerised tests	x	x	x	x
Falls self-efficacy	Falls Efficacy Scale-International questionnaire	x	x	x	X
Additional measures					
Anthropometry	Height, weight and body mass index	x	x	x	x
Body composition	Bioelectrical impedance (fat mass, fat-free mass and % fat)	x	x	x	x
Physical activity	Community Healthy Activities Model Programme for Seniors questionnaire	x	x	x	x
Falls-related injuries	Monthly calendar	Monthly			
Health and medical history	Lifestyle questionnaire	x	x	x	x
Dietary intake	Anti-Cancer Council Food Frequency Questionnaire	x	x	x	x
Adverse events^a^	Questionnaire and interview		x	x	x
Exercise programme compliance	Calculated from exercise cards	Collected every month			

^a^Adverse events will also be collected at 3 months.

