
### Statistical methods

Primary analyses will be conducted on an intention-to-treat basis using STATA statistical software release (STATA, College Station, TX, USA). Per protocol analysis will also be performed by including all participants who are at least 80% compliant to the exercise (as measured by the number of exercise sessions attended). Initially, descriptive statistics will be computed to compare the intervention and control groups on background variables and baseline measures. Imbalances on prognostic factors between the groups will be adjusted for during analyses. Calculation of QoL scores (SF-36 v2, AQol-6D) will utilise published ‘weightings’ most relevant to this population. Baseline measures and changes in outcome variables over the study period for each study arm will be presented as means (± SD) with 95% confidence intervals. The effect of the intervention on the primary outcome variables will be assessed using negative binomial regression, to account for the non-independence of multiple events for the same participants and to allow for over-dispersion [77]. To account for clustering, the negative binomial regression analysis will be carried out using the generalised linear mixed modelling approach, with observations clustered within retirement villages; village will be modelled as a random effect. Differences between the intervention and control groups on the secondary outcome measures will be examined using linear mixed models with assessment times clustered within individuals and individuals clustered within villages. Village and, where appropriate (as determined by the likelihood ratio tests) individuals, will be modelled as random effects. The secondary outcome variables will be checked for normality prior to analysis and transformed appropriately if necessary. For both primary and secondary outcomes, random effects will be computed utilising robust standard errors. For all outcomes, primary analyses will compare unadjusted differences between the study groups at each follow-up. Supplementary adjusted analyses, with adjustment for potential covariates (baseline values of relevant outcome, age, sex, use of medication, chronic conditions, falls history and other background variables that show imbalances between the intervention and control groups) will also be conducted.

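### Knee extensor force is divided by lower leg length to correct for the lever arm, but that correction requires multiplying by the lever arm

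*Protocol article*

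**What the plan says.** All elements of the measurement are in the protocol article under Isometric muscle strength. For the position, "participants will be seated with their hip and knee at an angle of 90" degrees. The force is read "with a strain gauge attached to a strap around the leg about 10 cm above the ankle joint". The quantity taken forward is "the maximal knee extensor strength (kg) of each leg", a force rather than a torque. For analysis it "will be expressed per unit of lower leg length to compensate for the length of the lever arm".

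The measure is listed in Table 2 as "Isometric knee extensor strength", at baseline, 6, 12 and 18 months, and the Secondary outcome measures section includes it among "isometric knee extensor, dorsi-flexor and hand grip strength, dynamic balance and reaction time, gait". Under Statistical methods, secondary outcomes are analysed with "linear mixed models with assessment times clustered within individuals and individuals clustered within villages", and for all outcomes "primary analyses will compare unadjusted differences between the study groups at each follow-up". No other section converts the force to a torque or gives a different rule for this measure.

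**The concern.** Expressing a quantity per unit of length means dividing by that length. The purpose given is to allow for the lever arm. A person with a longer lever arm produces a smaller force at the strap for the same knee torque, so the raw reading is already too low as a measure of torque. Dividing it by a length that is also larger in that person lowers it further. The stated operation and the stated purpose therefore point in opposite directions.

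There is a smaller mismatch in the same sentence. The divisor is the whole lower leg length, while the strap sits about 10 cm above the ankle, so the length used is not the lever arm itself.

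What is at stake is the meaning of a named secondary outcome. An analyst who follows the sentence produces a variable in kg per unit length that is neither force nor torque, and a reader told that it is corrected for the lever arm would misread it.

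**Working it through.** The article states no figure for this measure, so there is none to reproduce. The check is a moment balance.

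**Inputs from the document.** The force F is read in kg, the strap is about 10 cm above the ankle, the knee is at 90 degrees, and the planned score is F divided by lower leg length L.

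**Assumptions, not in the document.** The strap pulls roughly at right angles to the shank. The lever arm is d = L − 10 cm. Two people have the same torque, T = 80 Nm, and lower legs of 36 and 42 cm, so d = 26 and 32 cm.

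**Formulas.** T = F x 9.81 x d (d in m), so F = T / (9.81 x d). The planned score is F / L, which is proportional to T / (d x L). The lever-arm correction is F x 9.81 x d = T.

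**Results.**

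| Measure | 36 cm leg | 42 cm leg | Longer v shorter |
|---|---|---|---|
| Raw force (kg) | 80 / (9.81 x 0.26) = 31.4 | 80 / (9.81 x 0.32) = 25.5 | 26/32 = 0.81, 19% lower |
| Planned score (kg/cm) | 31.4 / 36 = 0.871 | 25.5 / 42 = 0.607 | 0.70, 30% lower |
| Force x lever (Nm) | 80 | 80 | no difference |

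On the log scale the gap grows from ln(0.8125) = −0.21 to ln(0.696) = −0.36, a factor of about 1.7.

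**Range.** With legs of 36 and 44 cm, raw force is 23.5% lower in the longer leg, the planned score 37.4% lower, force x whole leg length 6.5% lower, and force x lever 0% different. If the strap is taken to be at full leg length, the figures are 18.2% lower for raw force, 33.1% lower for the planned score, and 0% for force x leg length. The size depends on the assumed lengths. The direction does not, because for fixed torque F/L falls with length faster than F does.

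**If torque rises with leg length.** The example holds torque equal, which isolates the lever arm. Between real people, torque may increase with size. Let T be proportional to L to the power p. For 42 v 36 cm the torque ratio is (42/36)^p, and the planned-score ratio is 0.696 x (42/36)^p.

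| p | Torque | Planned score |
|---|---|---|
| 0 | 0% | −30% |
| 1 | +17% | −19% |
| 2 | +36% | −5% |
| 3 | +59% | +11% |

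The two are equally dependent on leg length, in opposite directions, when 2p x ln(42/36) = 0.36, that is p = 0.36 / (2 x 0.154), or about 1.2. Below that value the planned score varies more with leg length than torque does. Over the rest of the range shown it varies less.

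**Scale in an arm comparison.** Take p = 0, a mean leg of 39 cm (lever 29 cm) and an assumed chance difference of 0.5 cm between arms. Raw force shifts by about 0.5/29 = 1.7%, and the planned score by about 0.5/29 + 0.5/39 = 3.0%. The division adds about 1.3 percentage points.

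**The case against.** The strongest defence is that dividing strength by a body dimension is a form of size scaling, and that the document does not show such scaling to be harmful here. The table over p supports part of this: if torque rises steeply enough with leg length, the planned score depends less on body size than torque does. A reader might infer from the error that any difference in sex or height mix between arms, with about 15 villages randomised, enters the comparison with extra weight. The document does not support that. It holds only if torque is weakly related to leg length, and no such relation is given. A reader might also infer that the leg-length dependence doubles; in the worked example the factor is about 1.7.

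Other limits also stand:

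- The 30% figure compares two individuals, not two arms.
- The secondary outcomes are described as changes. Leg length is essentially constant within a person, so percentage change is the same for force, the planned score and torque.
- Randomisation by village leaves the contrast unbiased in expectation, and supplementary analyses adjusting for baseline value and sex are planned.
- No power statement in the Sample size section names this measure.
- The article may be loosely worded, with the calculation done differently in practice.

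None of this rescues the sentence. The purpose it gives is lever-arm compensation, not size scaling, and division cannot serve that purpose. If only the wording is wrong, the wording still has to change, because it is the only derivation the document gives.

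**Conclusion.** The point holds as an error of definition. The rule for knee extensor strength does the opposite of its stated purpose, and the resulting values cannot be read as lever-arm-corrected strength. For equal torque and assumed legs of 36 and 42 cm, a 19% artefact in raw force becomes 30% in the planned score, where the proper correction gives none. The direction rests only on the moment balance and a roughly perpendicular pull; the percentages rest on the assumed lengths.

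The point does not show bias in the treatment comparison, nor greater sensitivity to imbalance between arms, since the relation of torque to leg length is not given. The falls outcome and the sample size are untouched. Severity is low.

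**What to change.** Under Isometric muscle strength, define the outcome as knee extensor torque in Nm for each leg: maximal force in kg x 9.81 x knee-to-strap distance in m. Remove the expression per unit of leg length. If only lower leg length was recorded, use that length minus about 10 cm as the distance and say that it is a proxy, since the strap position is approximate and the article does not state the endpoints of the leg-length measurement.

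The cost is one line of derivation. Data already collected can be recalculated provided that leg length was recorded. The planned rule implies that it was, but neither Table 2 nor the anthropometry section lists it, so this should be confirmed and the measurement added there.

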#### Muscle function and performance

The Four-square step test (FSST), Timed up-and-go test (TUG), and choice stepping reaction time (CSRT) will be used to assess lower limb muscle function. Each of these tests will be performed in the participant’s own footwear.

The FSST provides a measure of dynamic balance and stepping speed in four directions [55]. Participants will be instructed to step forward, sideways, and backwards over four canes resting flat on the floor in a cross formation. The test begins with the participant moving first in a clockwise direction and returning in a counter-clockwise direction to the start square. Participants will be instructed to complete the task as quickly as possible without touching or stepping on the canes and, if possible, to face forward during the entire sequence. They will also be instructed to ensure that both feet make contact with the floor in each square. After 1 practice trial, participants will complete the test and the time (in seconds) taken to complete the sequence will be measured with a stopwatch and recorded as the final score. The FSST has been shown to discriminate between community-dwelling older adults with and without a history of falls [55]. The test has an 89% multiple falls sensitivity and an 85% specificity for non-fallers with a cut off score of greater than 15 seconds [55]. The test has been shown to have a high test-retest reliability of 0.98 [55].

The TUG test is a measure of dynamic balance using three commonly performed functional activities of daily living: standing and sitting, walking, and turning [56]. Participants will be seated in a chair (height 45 cm) that will be placed at the end of a marked 3-meter walkway. On the command ‘go’, participants will be instructed to stand up, walk at a comfortable speed for 3 meters, turn back to the chair and sit down. The test will be performed under both single- and dual-task conditions. The dual-task condition will involve participants completing the task while counting backwards in threes from a randomly selected number. All participants will be given a practice trial and one test run. Participants who require a usual indoor walking aid (cane or walker) will perform the test with the use of their aid. A stopwatch will be used to record the time taken (in seconds) to complete each test. Prior to completing the dual-task TUG test, the participants cognitive ability while seated will be assessed by asking them to count backwards in threes from a random number. The time taken to complete 10 subtractions from this random number will be recorded. The number of errors that occur during the seated and dual-tasking test will be recorded for all participants. ‘Dual-task cost’, which represents the change in performance with the addition of a second task, will be calculated as:$$ \mathrm{Dual}\hbox{-} \mathrm{task}\ \mathrm{TUG}\ \mathrm{performance}\ \hbox{-}\ \mathrm{single}\ \mathrm{TUG}\ \mathrm{task}\ \mathrm{performance}/\mathrm{Single}\ \mathrm{TUG}\ \mathrm{task}\ \mathrm{performance} \times 100 $$

The TUG test has an interrater reliability of 0.99 and an 87% prediction rate for identifying fallers and non-fallers when performed with a cognitive dual task [57].

Choice stepping reaction time (CSRT) is a measure of a participant’s ability to step as quickly as possibly onto one of four foot panels [58]. This test has been shown to be an independent predictor of falls risk [58]. Participants will stand on a non-slip choice reaction mat (0.8 × 0.8 m) that contains 4 rectangular panels (32 × 13 cm), 1 in front of each foot and 1 to the side of each foot [58]. One panel per trial will illuminate in a random order, and participants will be instructed to step onto the illuminated panel as quickly as possible, using the left foot only for the two left panels (front and side) and the right foot only for the two right panels. Following a practice trial, participants will complete a single trial that will involve 12 target stepping actions in which 12 green arrows will appear in a random sequence. Following this trial, participants will complete the same activity but with the addition of a dual task. For this trial, participants will be asked to step when a green arrow appears and to not step when a purple arrow appears. A total of eight green panels and four purple panels will be displayed in a random sequence. CSRT will be measured as the time period between the illumination of an arrow and the foot making contact with it, and the average reaction time (in ms) will be recorded. In addition, the total time will be subdivided into: 1) the reaction time measured from the illumination of the arrow to movement initiation (lift off), and 2) the movement time measured from movement initiation to foot contact with the arrow/mat (‘step down’).

#### Functional gait

Gait function will be assessed using the ProtoKinetics Zeno system (ZenoMetrics LLC, Peekskill, NY, USA), which comprises a computerised walkway with the ProtoKinetics Movement Analysis Software (PKMAS) programme. The ProtoKinetics Zeno walkway system is a 2-foot wide by 16-foot long mat that contains a 16-level pressure sensing pad with 18,432 pressure sensors arranged in a grid pattern with a spatial resolution of 0.5 cm and a sampling frequency of 120 Hz. Participants will be asked to perform 18 trials on the Zeno system, wearing comfortable footwear, at their preferred walking speed, and with their usual indoor walking aid if required. Three different gait conditions will be assessed: 1) simple walking; 2) walking while counting backwards in 7s from a computerised derived random number between 70 and 99 (cognitive dual task), and 3) walking while carrying a tray whilst balancing a ball in a target (motor dual task). For the cognitive and motor dual task, the number of errors in counting backwards and the number of times the ball deviates from the centre of the target will be recorded. Motor dual-task trials will not be completed by those participants requiring an indoor walking aid. For each walking trial, all participants will start standing 1 m behind the walkway, and on the command ‘go’ they will walk the length of the Zeno mat to a cone that will be placed 1 m past the end of the walkway. All participants will be given standardised verbal instruction followed by one practice trial for each walking condition. Participants will not be given any instruction to prioritise attention to either the dual task or walking. The following gait parameters will be calculated using the mean of the three trials: gait velocity (m/s), cadence (steps/minute), step length (cm), double support time (seconds) and stride width (cm). ‘Dual-task cost’, which represents the change in performance with the addition of a second task, will be calculated as:$$ \mathrm{Dual}\hbox{-} \mathrm{task}\ \hbox{-}\ \mathrm{single}\hbox{-} \mathrm{task}\ \mathrm{walking}/\mathrm{Single}\hbox{-} \mathrm{task}\ \mathrm{walking} \times 100 $$

In addition, we will quantify each participant’s cognitive and motor ability whilst not undertaking a secondary task. Each participant will be asked to count backwards aloud by 7s while standing still. Once ten subtractions have been completed, the time taken and the number of errors will be recorded. Similarly, each participant will be asked to balance the ball in the centre of the tray for 20 seconds while standing still. The number of times the balls deviates from the centre of the target will be recorded. The order of the single and dual-task conditions will be randomised across participants.

#### Instrumental Activities of Daily Living (IADL)

Instrumental Activities of Daily Living (IADL) will be assessed using the Lawton IADL questionnaire [59], which is widely used to assess independent living skills. The tester rates the participant across eight functional abilities, including use of the telephone, shopping, food preparation, housekeeping, laundry, mode of transport, taking medications and handling finances. Participants are scored according to their highest level of functioning for each category. A summary score ranges from 0 (low function, dependent) to 8 (high function, independent).

